## **11.5 Criteria for Toxicity**

- 11.5.1 Acute toxicity monitoring:** Acute side effects ( $\leq 90$  days of treatment start) will be documented using the using the NCI Common Toxicity Criteria version 2.0.
- 11.5.2 Late toxicity monitoring:** Renal and GU toxicities will be evaluated and graded according to the NCI Common Toxicity Criteria version 2.0. All other late ( $> 90$  days from RT start) side effects will be evaluated and graded according to the RTOG Late Radiation Morbidity Scoring Scale (*Appendix IV*).

## **11.6 Criteria for Local Control**

- 11.6.1 PSA failure** is defined as having 3 consecutive elevations of post-treatment PSA or starting hormones after one or more elevations in post-treatment PSA but before three consecutive elevations are documented. The failure day is the midpoint between last non-rising PSA and first PSA rise. The ASTRO definition of rising PSA will be used. The presence of palpable disease must be recorded on the data collection forms for initial and follow-up evaluations of the patient. All PSA levels done during a follow-up interval will be recorded on the data forms.
- 11.6.2 Clinical criteria** for local failure are progression (increase in palpable abnormality) at any time, failure of regression of the palpable tumor by two years, and redevelopment of a palpable abnormality after complete disappearance of previous abnormalities. Needle biopsy is recommended.
- 11.6.3 Histologic criteria** for local failure are presence of prostatic carcinoma upon biopsy and positive biopsy of the palpably normal prostate more than two years after the start of treatment.

## **11.7 Criteria for Nonlocal Failure**

Other types of failure will be documented as follows:

- 11.7.1** Distant metastasis will be documented if clinical or bone scan evidence is demonstrated. Ultrasound evaluation of the prostate with needle biopsy as indicated by the findings is recommended at the time distant metastasis is reported.
- 11.7.2 Time to Distant Failure:** The time to distant failure will be measured from the date of randomization to the date of documented regional nodal recurrence or distant disease relapse. Patients with evidence of biochemical failure, but a negative prostate biopsy, will be considered as distant failure only.
- 11.7.3 Disease-Specific Survival:** Disease-specific survival duration will be measured from the date of randomization to the date of death due to prostate cancer. Causes of death may require review by the study chair or their designee. Death due to prostate cancer will be defined as:
- 11.7.3.1** Primary cause of death certified as due to prostate cancer.
- 11.7.3.2** Death in association with any of the following conditions:
- Further clinical tumor progression occurring after initiation of "salvage" anti-tumor (*e.g.*, (*androgen suppression*) therapy.
  - A rise (*that exceeds 1.0 ng/ml*) in the serum PSA level on at least two consecutive occasions that occurs during or after "salvage" androgen suppression therapy.
  - Disease progression in the absence of any anti-tumor therapy.
- 11.7.3.3** Death from a complication of therapy, irrespective of disease status.
- 11.7.4 Overall Survival:** Survival duration will be measured from the date of randomization to the date of death from any cause. A post-mortem examination will be performed whenever possible and a copy of the final post-mortem report will be sent to RTOG Headquarters.

## **12.0 DATA COLLECTION (6/12/14)**

*(NRG Oncology, [name] [contact])*

### **12.1 Summary of Data Submission (9/18/03) (4/18/06)**

| Item                                                 | Due                                                                                                                   |
|--------------------------------------------------------------------|-------------------------------------------------------------------------------------------------------------------------------------|
| Demographic Form (A5)                                              | Within 2 wks of study entry                                                                                                         |
| Initial Evaluation Form (I1)                                       |                                                                                                                                     |
| Pathology Report (P1)                                              |                                                                                                                                     |
| Slides/Blocks (P2)                                                 |                                                                                                                                     |
| International Index of Erectile Function Questionnaire [PQ]        |                                                                                                                                     |
| Functional Alterations due to Changes in Elimination [FA]          |                                                                                                                                     |
| The Spitzer Quality of Life Index [SP]                             |                                                                                                                                     |
| 
Preliminary Dosimetry Information:                      | 
See Section 12.2                                                                                                                |
| 
Final Dosimetry Information:                            | 
See Section 12.2                                                                                                                |
| Radiotherapy Form (T1)                                             | Within 1 wk from end of RT                                                                                                          |
| (Copy to RTOG HQ and ITC)                                   |                                                                                                                                     |
| 
Initial Follow-up Form (FS)                                    | 
90 days from start of treatment                                                                                                 |
| Functional Alterations due to
Changes in Elimination [FA]       |                                                                                                                                     |
| The Spitzer Quality of Life Index [SP]                             |                                                                                                                                     |
| 
Follow-up Form (F1)                                            | 
6, 9, 12 months in year 1; q 3 months in year 2; q 6 months x 3 years, then annually; Also at progression/relapse and at death. |
| 
International Index of
Erectile Function Questionnaire [PQ] | 
6 and 12 months from start of treatment; then annually through year 5                                                           |
| 
Functional Alterations due to
Changes in Elimination [FA]   | 
6, 9, 12, 18, and 24 months; then every 6 months through year 5                                                                 |
| The Spitzer Quality of Life Index [SP]                             |                                                                                                                                     |
| 
Autopsy Report (D3)                                            | 
As applicable                                                                                                                   |

### **12.2 Summary of RT QA Requirements (submit to Washington University via ATC website at <http://atc.wustl.edu>) (11/24/04)**

|                                                                                                         |                              |
|---------------------------------------------------------------------------------------------------------|------------------------------|
| Preliminary Dosimetry Information:                                                        | Within 1 week of start of RT |
| Digital Patient Submission Information Form (T2)                                                        |                              |
| CT data, critical normal structures, all GTV, CTV and PTV contours                                      |                              |
| Simulation films and/or digital film images for all initial treatment fields and orthogonal set up pair |                              |
| First day port films (or digital images) of all initial treatment fields and orthogonal set up pair     |                              |
| Digital beam geometry for initial and boost beam sets                                                   |                              |
| Doses for initial and boost sets of concurrently treated beams                                          |                              |

Digital DVH data for all required critical normal structures, GTV, CTV, and PTVs for total dose plan  
Hard copy isodose distributions for total dose plan as described in the QA Guidelines

**Final Dosimetry Information:**

Within 1 week of RT end

Copy of Radiotherapy Form (T1)  
Daily Treatment Record  
Simulation films and/or digital film images for all  
(*or digital images*) of all boost treatment fields  
and orthogonal set up pair  
First day port films of all boost treatment fields and  
orthogonal setup pair  
Modified digital patient data as required through  
consultation with Image Guided Therapy QA Center

**12.2.1**     *For Mail or Federal Express* (9/18/03) (4/18/06) (7/10/07)

**[name]  
QA Dosimetry Specialist  
Image-Guided Therapy Center (ITC)  
Washington University School of Medicine  
[name]  
[name]  
[name]; [contact]**

**12.2.2.**     *To send over Internet or using magnetic tape* (9/18/03)

Digital data submission may be accomplished using magnetic tape or the Internet. For network submission, the *ftp* account assigned to the submitting institution shall be used and *e-mail* identifying the data set(s) being submitted shall be sent to:

|                                                                |
|----------------------------------------------------------------|
| [contact] |
|----------------------------------------------------------------|

For tape submission, please contact the ITC about acceptable tape types and formats.

## 13.2 Sample Size

**13.2.1** *Stratification:* Patients will be stratified before randomization with respect to PSA and Gleason score: Gleason score 2-6 and PSA  $\geq 10$  but  $< 20$  vs. Gleason score 7 and PSA  $< 15$ , and Radiation Modality: 3D-CRT vs. IMRT. The treatment allocation scheme described by Zelen will be used because it balances patient factors other than institution. Patients will be randomized to MTD 3D-CRT or IMRT dose (79.2 Gy) vs. standard dose 3D-CRT or IMRT (70.2 Gy). (9/18/03)

**13.2.2** *Sample Size Derivation:* The sample size calculations will address the specific primary hypothesis that the maximally tolerated dose of 3D-CRT/IMRT delivered to patients with localized adenocarcinoma of the prostate will result in a hazard reduction of 23% in the mortality rate. Roach et al. identified four prognostic risk groups using independent predictors of death: combined Gleason score (*centrally reviewed*), T stage, and pathologic lymph node status. These groups were defined by observing the correlation between these factors and disease-specific survival. The five, ten and fifteen-year overall survival rates by risk group are presented in Table 1 below. Based on these risk groups, the probability of surviving in a five-year interval (1-5, 6-10, 11-15) is shown in Table 2. A preliminary analysis of RTOG 94-08, which is a two-arm study of endocrine therapy used as a cytoreductive and cytostatic agent prior to radiation therapy (RT) in locally confined adenocarcinoma of the prostate, showed a five-year overall survival rate of 74% for patients with clinical stage T1b-T2b, combined Gleason scores 2-6 and PSA  $< 20$  treated with radiation therapy alone. Forty-four percent of the men entered on RTOG 94-08 had a combined Gleason score between 2-6 and a PSA value  $\geq 10$  but  $< 20$  while 56% had a Gleason of 7 and PSA  $< 15$ . In light of these data, the survival estimates based on Roach et al. risk group two were used for the sample size calculations. The five and ten-year overall survival rates used were 80% and 48%, respectively. The hazard rates of the control arm are assumed to be constant within each five-year interval (1-5, 6-10, and 11-15) and they are 0.0446, 0.1022, and 0.1386, respectively. Five interim significance tests and a final test are planned. Early testing will employ a nominal significance level of 0.001 while a level of 0.020 will be used at the final analysis to preserve a 0.025 level for the study. Using Lakatos' method for time-dependent mortality rates, 715 deaths are required to detect a survival benefit translating into a hazard ratio ( $\Delta$ ) of 1.3 with 90% statistical power using a one-sided test at a level of significance of 0.025. This level of 0.025 is the same as a level of significance that would be required for a two-sided test of significance at 0.05 to show the experimental arm is better than the control arm. Using the projected hazard rates for each five-year interval, we will require a total sample size of 1410 to be accrued uniformly over five years with an additional eight years of follow-up. Guarding against an ineligibility or lack-of-data rate up to 8%, **the final targeted accrual for this study will be 1520 cases.** Some of the secondary endpoints that will be evaluated are PSA failure, disease-specific survival, and quality-adjusted survival. The planned PSA failure analysis after the 7th year is discussed in more detail in section 13.4.3.2. (9/18/03)

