**13.4.3 *Significance Testing for Early Termination and Reporting:***

**13.4.3.1 *Primary Endpoint: Overall Survival***

Five interim significance tests of treatment difference are planned. The first interim analysis will be performed for the first RTOG semi-annual meeting after the 4th year of accrual. After the 5th year, it is projected that 100% of the target sample size has been achieved. The second interim analysis will be performed for the first RTOG semi-annual meeting one year after the last patient has been randomized. The third, fourth, and fifth interim analysis will be performed approximately eight, ten, and twelve years, respectively, from the start of the trial. The results will be reported to the NRG Oncology Data Monitoring Committee (DMC) with the treatment arms blinded.

The maximum number of deaths required for the study is 715. Under the alternative hypothesis given above, the projected numbers of deaths at the time of these five interim analyses are approximately 85, 186, 320, 478, and 640. The corresponding nominal significance level for each interim analysis will be 0.001. If the difference is significant at that level, the study statistician will recommend to the DMC that the randomization be discontinued (*if applicable*) and the study be considered for early publication.

At each planned interim analysis, the p-value from the log-rank test for assessing treatment efficacy, and the conditional power for the alternative hypothesis given the observed data will be reported to the NRG Oncology DMC. A low conditional power indicates a small probability of a significant treatment effect if future follow-up events are assumed to follow the same distribution under the alternative hypothesis. The responsible statistician may recommend early reporting of the results and/or stopping the trial if the treatment effect, with respect to overall survival, is highly significant, i.e. the p-value is less than the nominal value specified in a sequential design, or if the conditional power is less than 10%. Before making such a recommendation, the accrual rate, treatment compliance, safety of the treatments, and the importance of the study are also taken into consideration with the p-value and conditional power. The DMC will then make a recommendation about the trial to the group chair.

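### The final level of 0.020 is a valid but conservative split: about 0.003 of the stated one-sided 0.025 is left unspent, and a group-sequential final level near 0.0233 would recover it

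*Protocol*

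**What the plan says.** Section 13.2.2 sets the primary comparison "using a one-sided test at a level of significance of 0.025". It states that "Five interim significance tests and a final test are planned", and that "a level of 0.020 will be used at the final analysis to preserve a 0.025 level for the study". A methods reference is cited for the scheme, but no derivation of 0.020 is given.

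Section 13.4.3.1 repeats the interim level: "The corresponding nominal significance level for each interim analysis will be 0.001". It gives the timing: "the projected numbers of deaths at the time of these five interim analyses are approximately 85, 186, 320, 478, and 640", and "The maximum number of deaths required for the study is 715". The interim statistic is the log-rank test ("the p-value from the log-rank test for assessing treatment efficacy"). Section 13.4.4 tests the primary hypothesis at the main analysis with a Cox model that includes the stratification factors. Section 13.4.5 adds futility bounds at the third, fourth and fifth looks.

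**The concern.** The final level is exactly what remains after subtracting 0.001 five times from 0.025. A sum of nominal levels is an upper bound on the chance of at least one false crossing. The bound is loose when the same deaths enter every later look, because trials that cross early under the null are largely the ones that would also cross later. The true joint error is then below 0.025, and the final threshold is stricter than the stated level requires.

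At stake is a narrow band of final results. A trial planned to run thirteen years could end with a p-value that its own 0.025 level would accept and its written rule would reject.

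**Working it through.** **Inputs.** Overall level 0.025 one-sided, interim level 0.001, final level 0.020 and hazard ratio 1.3 (13.2.2); deaths 85, 186, 320, 478, 640 and 715 (13.4.3.1).

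**Assumptions.**
- The interim 0.001 is one-sided, like the overall test. The protocol does not say so, but the P values in the futility table of 13.4.5 are one-sided: Z = 1.124 is paired with 0.131.
- Futility bounds are non-binding.
- Allocation is 1:1 (needed for power only).
- One log-rank-type statistic is used at all six looks.

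**Step 1, reproduce 0.025.** 5 × 0.001 + 0.020 = 0.025, so the stated level is the additive sum. Even independent looks would give slightly less: 1 − 0.999⁵ × 0.98 = 0.0249.

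**Step 2, joint error.** On the death scale, the correlation between looks i and j is √(Dᵢ/Dⱼ). Between the fifth look and the final it is √(640/715) = 0.95. The critical values are z = 3.090 at each interim and 2.054 at the final. Recursive numerical integration gives the null probability of a first crossing at each look:

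| Look | Deaths | First crossing under the null |
|---|---|---|
| 1 | 85 | 0.00100 |
| 2 | 186 | 0.00086 |
| 3 | 320 | 0.00076 |
| 4 | 478 | 0.00067 |
| 5 | 640 | 0.00058 |
| Final | 715 | 0.01793 |

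The interims spend 0.0039 in place of 0.005, and the total is 0.0218. A simulation of 8 million null trials also gives 0.0218. The unspent part is 0.025 − 0.0218 = 0.0032, about 13% of 0.025.

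**Step 3, the level that spends 0.025.** With the interims unchanged, a final level of 0.0233 (z = 1.990) brings the total to 0.0250.

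**Step 4, effect on the final test.** The critical hazard ratio (experimental/control) is exp(−2z/√715), with √715 = 26.74.
- At 0.020: exp(−2 × 2.054/26.74) = 0.858.
- At 0.0233: exp(−2 × 1.990/26.74) = 0.862.

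**Step 5, power at 715 deaths.** For a single test, power is Φ(ln(1.3) × 26.74/2 − z) = Φ(3.508 − z). This is Φ(1.454) = 92.7% at 0.020 and Φ(1.518) = 93.5% at 0.0233. With the interim looks included, the figures are 92.8% and 93.6%, a gain of 0.8 points.

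**Step 6, sensitivity.**

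| Variation | Joint one-sided error |
|---|---|
| Six equally spaced looks | 0.0216 |
| Interim 0.001 two-sided (0.0005 per side) | 0.0208 |
| Futility bounds treated as binding | 0.0211 |

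The total stays below 0.025 in each. Under the two-sided reading, the final level that spends 0.025 is 0.0242.

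**The case against.** The strongest objection is that nothing here is wrong. A level is a ceiling: 0.0218 does not exceed 0.025, so the claim to preserve 0.025 is true. That stands, and it limits the point to efficiency.

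The additive split also has a merit. The looks are set by calendar and the death counts are only projected, while the split holds whatever the information fractions turn out to be. It also holds although the interims use the log-rank test and the final analysis a covariate-adjusted Cox model. This stands too, and it means that 0.0233 is an approximation unless one family of statistic is used throughout. A level computed from the observed death counts deals with the timing.

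A further objection is that 13.4.5 says the early interim analyses are complete, so relaxing the final threshold now follows looks at efficacy data by the data monitoring committee. The level depends on death counts and not on the observed effect, so the change can be made without bias, but it must be made blind and documented.

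A reader might infer more than the documents support:
- **That the authors treated the looks as disjoint or forgot their correlation.** The protocol gives no derivation, and an additive bound is valid under any correlation.
- **That follow-up could be shortened.** Single-test deaths for 90% power, 4(z_α + 1.2816)²/ln²(1.3), are 647 at 0.020 and 623 at 0.0233. Both are below the planned 715, so with 715 fixed no time is saved.
- **That the trial loses its planned power.** It keeps 92.8% against a stated 90%.

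**Conclusion.** The point holds as a minor inefficiency. With the interim 0.001 one-sided and looks at the planned deaths, the rule spends about 0.0218 of 0.025 (0.0208 if 0.001 is two-sided). The practical consequence is confined to a final one-sided p between 0.020 and about 0.0233, or a hazard ratio between about 0.858 and 0.862. Such a result would be declared negative although the stated level permits the claim.

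The error figures do not depend on the assumed treatment effect; the 0.8-point power gain does, through the hazard ratio of 1.3. The exact final level depends on the sidedness of 0.001, the observed death counts and the use of a common test statistic. That the rule leaves some of the 0.025 unspent held under every variation checked.

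**What to change.** Keep 0.001 at each interim and state whether it is one- or two-sided. Replace 0.020 in 13.2.2 with the level from the group-sequential calculation that brings the joint one-sided error to 0.025 at the observed death fractions: about 0.0233 at the planned counts, or 0.0242 if 0.001 is two-sided. Use the same family of test statistic at every look, or note that the level is approximate because the interims use the log-rank test and the final analysis a Cox model. Have the level fixed before the final data are seen, from death counts alone, by someone blind to the comparative results.

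The cost is a short amendment and a standard calculation. It adds no patients, deaths or looks. The actual error rises from about 0.0218 to the stated 0.025, in exchange for about 0.8 points of power.

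If the sponsor prefers 0.020, one sentence is enough: say that it is deliberately conservative and that the actual level is about 0.022.
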